### Intervention

Usual physiotherapy management for each child in the study comprises 3 components:
***Multi-disciplinary (MDT) Review & Individual Exacerbation Plan:***
As recommended by Australian and New Zealand clinical practice guidelines [1], all participants in both groups will receive one face-to-face physiotherapy session in a multidisciplinary CF clinic approximately every three months. Each child with CF is advised on an individualised exacerbation plan where minor exacerbations can be managed at home with parental supervision.
***Outpatient physiotherapy services (OPS)***
**:**
Apart from these routine check-ups, OPS may be clinically indicated on an individual patient basis. Timing and frequency of OPS will be determined by the child’s treating physiotherapist according to clinical indicators which will be identical for children in both treatment arms. If OPS is required, it will be delivered in a mode according to the group that the child has been randomised to - Usual OPS or CyFiT OPS. Physiotherapy in both arms will be delivered by the same physiotherapy team. Only the mode of delivering OPS will differ according to group allocation (face-to-face or telehealth).
**Escalated Care with Hospital Admission:**
If a child in either group presents with any clinical indicator for admission to the hospital, then the child will receive face-to-face physiotherapy by hospital physiotherapy staff during these periods of inpatient admission as per routine clinical practice.

#### Usual outpatient physiotherapy services (usual OPS)

Participants allocated to the Usual OPS group may receive OPS as a combination of face-to-face, telephone, and/or telehealth follow up as determined at the time by the treating physiotherapist. Each review may involve any or a combination of the child’s home exercise program, airway clearance techniques, use and maintenance of therapy equipment, and support for adherence. If telehealth is included as an intervention mode, this will be delivered through the standard Queensland Health Telehealth Network (QH Telehealth). The QH telehealth system enables physiotherapists to connect via real-time videoconferencing. Physiotherapists may choose to utilise QH Telehealth to replace some face-to-face reviews to better suit patient schedules or to provide video feedback (e.g. seeing child demonstrating airway clearance techniques) that is otherwise not possible through a telephone review.

#### CyFiT outpatient physiotherapy (CyFiT OPS)

Participants allocated to the CyFiT OPS group will receive OPS via telehealth as the primary mode of delivery. In this group, a different telehealth system called eHAB® will be used. The eHAB® system was developed at The University of Queensland for specialised telerehabilitation. When using eHAB® with an individual child, clinicians can access additional digital functions not available via existing QH Telehealth System, such as real-time image/video sharing, whiteboard for drawing diagrams, measurement tools for looking at various joint ranges of motion across the body and session recording that will facilitate an enhanced telehealth experience compared to videoconferencing alone. In addition, eHAB® enables clinicians to work with groups of children, for example to host real-time multipoint video conferences to deliver virtual group-based sessions.

In addition to having access to the eHAB® telehealth system for CyFit OPS, children allocated to the CyFiT group will be asked to wear a consumer-based wrist-worn activity tracker, Garmin Vivosmart3® (Garmin Ltd., Lenexa, KS, USA), during the 12-month intervention period. Children can utilise all functions available on the activity tracker. Health-related data (such as heart rate variability, sleep duration, steps, distance travelled, energy expenditure) will also be monitored by the treating team to inform physiotherapy practices in exercise prescription and in telehealth sessions (with access to near-real-time physiological information).

##### Integration of CyFiT into current model of care

Physiotherapists will have access to health-related data collected from wrist-worn activity trackers. This information can be used to support clinical decision making by physiotherapists, to initiate OPS check-up (in the form of telehealth) and feedback to the multidisciplinary team. From the patient’s perspective, health-related data displayed on their activity trackers may assist them in self-managing their therapy.

#### Clinician support system

This trial will utilise a web-based clinician support system developed by The University of Queensland. This system will enable physiotherapists to monitor health-related data collected from activity wristbands, organise online group-based sessions and engage with families remotely for children in CyFiT OPS. Children with sudden changes to health-related data will be automatically highlighted to clinicians via the clinician support system. Changes in health-related data may then be used by physiotherapists to assist in clinical decision-making and initiate additional follow-up.

### Study outcomes

#### Study duration

Each child will be involved in the trial for 18 months, including a 12-month intervention period where the child is randomised to either Usual OPS or CyFiT OPS, followed by a 6 month follow up period where all participants will revert to Usual OPS and use of QH Telehealth services (as indicated). In CyFiT OPS, the intervention period can be further divided into phase one (0-6 months) and phase two (6-12 months) (see below). All outcome measures will be assessed (i) at baseline, (ii) after 6 months, (iii) after 12 months - end of intervention, and (iv) at 18 months – 6 months after the end of intervention, for both groups.

##### Phase one

Phase one is an opportunity for children and clinical physiotherapists to familiarise themselves with technology (i.e. activity wristbands and eHAB®). During this period, children will only be participating in one-to-one OPS via telehealth in the intervention group as clinically indicated. Treating physiotherapists will have access to health-related data via supplier web portal. Health-related data collected during phase one will enable the research team to derive statistical models to monitor children’s health and better assist clinical decision making.

##### Phase two

Phase two occurs in the last 6 months of the 12-months intervention. In addition to one-on-one OPS via telehealth, physiotherapists can refer children in the CyFiT OPS group to an online group-based exercise class. Group sessions will be delivered using the eHAB® system. In this phase, health-related data and risk score will be visualised using the clinician support system, and this information will be used by physiotherapists to assist in clinical decision making, such as initiating OPS check-ups.

#### Primary outcome measure

##### Cystic fibrosis questionnaire – Revised (CFQ-R)

The CFQ-R is a valid and reliable quality of life measure for children with CF from 6 years of age (A. L. [18]). The score is positively correlated with pulmonary function in adolescents with CF [19]. It includes nine quality of life domains: physical (8 items), role limitation, vitality (5 items), emotional (5 items), social (6 items), body image (3 items), eating disturbances (3 items), treatment burden (3 items), and health perceptions (3 items); as well as three symptom-based scales: weight (1 item), respiratory (6 items), digestion (3 items). All items are scored on a 4-point Likert Scale (1 = Very true/Always to 4 = Not at all true/Never). Scores for each domain will be analysed individually.

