### Study design

This is a single centre, prospective parallel randomised controlled non-inferiority trial with a 1:1 allocation across two treatment arms: Usual OPS and CyFiT OPS. Children receiving Usual OPS will serve as the control group for the trial.

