### Sample size

The minimum clinically important difference (MCID) for the CFQ-R has been previously calculated for people with CF who are medically stable (using distribution/Smallest Error Measurement method) as 6.1 (A. L. [24]). Standard deviation on CFQ-R improvement (treatment burden) has been previously reported as 8.6 [25]. A power of 0.9 and an alpha value of 0.025 has been chosen for this trial. Using this information, sample size for each group has been calculated to be 42 participants per group [26]. To allow for patient dropout, a total of 55 participants per group will be recruited.

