### Data analysis

All statistical analyses will be performed using SPSS 24 (IBM Corp., Armonk, NY, USA). Data will be analysed on an intention-to-treat basis. Generalised linear models will be used to determine any differences between repeated outcome measures across Usual OPS and CyFiT OPS. Missing data will be handled using predictive mean matching imputations using five observed cases for each missing value and a total of five imputed data sets will be pooled as the final result [27]. Statistical significance will be set at *p* < 0.05.

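### The primary outcome is every CFQ-R scale analysed separately, with no lead scale or success rule, but the sample size covers one comparison on one scale

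*Protocol article*

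**What the plan says.** The Study design section describes a "single centre, prospective parallel randomised controlled non-inferiority trial" "with a 1:1 allocation across two treatment arms".

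Under Primary outcome measure, the only instrument named is the CFQ-R. Of its content the article says "It includes nine quality of life domains", and then "as well as three symptom-based scales: weight (1 item), respiratory (6 items), digestion (3 items"). The section closes with "Scores for each domain will be analysed individually". It singles out no domain or total score and does not say how many scales must show non-inferiority.

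The Sample size section makes one calculation. Its difference is general to the instrument: "The minimum clinically important difference (MCID) for the CFQ-R has been previously calculated for people with CF who are medically stable", with the value 6.1. Its SD belongs to one domain: "Standard deviation on CFQ-R improvement (treatment burden) has been previously reported as 8.6". Power is 0.9, alpha is 0.025 (sidedness not stated), and the result is 42 per group, raised to 55 for dropout.

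The Data analysis section gives one general threshold: "Statistical significance will be set at *p* < 0.05". The Study duration section schedules assessments at baseline, 6, 12 and 18 months and does not mark one as primary.

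**The concern.** A non-inferiority trial needs one rule that turns its primary data into a yes or a no. Here the primary outcome is a set of nine or 12 scores, while the design calculation treats it as a single score. The Background section asks one question, whether the telehealth service is non-inferior on health outcome and quality of life, and says that a positive answer would bring it into the existing service. The reader cannot tell which results would count as that answer.

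The missing rule decides what the trial's operating characteristics are. If one passing scale is enough, a false non-inferiority claim is much more likely than 2.5%. If every scale must pass, the chance of success for a truly equivalent service is well below 90%. The article states one power and one alpha as if this choice did not arise.

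**Working it through.** **Inputs.** From the Sample size section: difference 6.1 (used as the margin), SD 8.6, power 0.9, alpha 0.025, 42 per group (55 recruited). From the primary outcome section: k = 9 domains, or 9 + 3 = 12 with the symptom scales. Assumed, because the article gives no values: correlation between scale-level test statistics of 0, 0.5 or 0.8 (equal for all pairs), and SDs of 10, 12 and 15 for other scales. The true difference is taken as zero when computing power.

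**1. The plan's own figure.** n per group = 2 × SD² × (z₀.₉₇₅ + z₀.₉₀)² / margin² = 2 × 8.6² × (1.960 + 1.282)² / 6.1² = 41.8, rounded up to 42. This matches the article exactly with alpha read as one-sided 0.025. (Two-sided 0.025 would give 50; one-sided 0.05 would give 35.) The normal-approximation power at 42 is 90.2%. The stated power and alpha are therefore right for one scale with SD 8.6 and margin 6.1.

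**2. If any one scale suffices.** Suppose the true difference is at the margin on every scale, and each is tested at one-sided 0.025. Under independence, the chance of at least one false claim is 1 − 0.975^k:
- k = 9: 1 − 0.975⁹ = 20.4%
- k = 12: 1 − 0.975¹² = 26.2%

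With equally correlated normal test statistics:

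| Scales | Correlation 0 | 0.5 | 0.8 |
|---|---|---|---|
| 9 | 20% | 13% | 8% |
| 12 | 26% | 16% | 9% |

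**3. If all 12 must pass.** The false-claim rate stays at or below 0.025. Grant SD 8.6 and margin 6.1 on every scale. The standardised distance to the margin is 6.1 / (8.6 × √(2/n)), which is 3.25 at n = 42 and 3.72 at n = 55. Per-scale power is Φ(3.25 − 1.96) = 0.902 and Φ(3.72 − 1.96) = 0.961. Under independence, joint power is 0.902¹² ≈ 29% and 0.961¹² ≈ 62%. With correlation:

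| n per group | Correlation 0 | 0.5 | 0.8 |
|---|---|---|---|
| 42 | 29% | 57% | 73% |
| 55 (no loss) | 62% | 77% | 87% |

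No cell reaches 90%.

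**4. If another single scale were primary.** The scales run from one item to eight, so a common SD cannot be presumed. With margin 6.1 and 42 per group, the t-based power is 79% at SD 10, 63% at SD 12 and 45% at SD 15. At SD 8.6 the same t-based calculation gives 89%, so the fall comes from the SD and not from the method.

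**The case against.** The strongest reply is that the sample size is arithmetically sound and that an unseen SAP may hold a hierarchy or a multiplicity procedure. Both parts have force. A reader might infer that neither the stated power nor the stated alpha holds at all. The article does not support that: both hold for treatment burden alone if 8.6 and 6.1 are right for it. Nor does any one success rule break both figures, since the any-scale rule inflates alpha and the all-scales rule lowers power. The absence of a multiplicity procedure from a condensed article is also no finding in itself, and the general p < 0.05 is not a statement that the primary scales will be tested unadjusted.

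A reader might further infer that the favourable domain could be picked after the results are seen. The text commits to analysing every domain, so selective choice is a possibility that the wording leaves open and not something that it plans.

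Three limits on size also stand. The closing sentence speaks of domains, so nine is the more literal count. Subscales of one questionnaire answered by the same child are unlikely to be independent, so the zero-correlation column is an extreme. The 42 is the number left after about 24% loss (1 − 42/55), and power is better if retention is better.

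What remains is protocol content. Which variable is primary is fixed here, and it does not match the calculation that sizes the trial. An SAP could add a rule, but the two sections would still need to be brought into line.

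**Conclusion.** The point holds as a mismatch between the primary outcome and the sample size, and it should be corrected before analysis. The 42 per group is right for one scale. The 90% power and 0.025 alpha cannot be attached to the overall non-inferiority conclusion until a success rule or a single primary scale is stated.

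Even the mildest case examined (nine scales, correlation 0.8) puts the any-scale false-claim rate at about three times nominal. The mildest all-scales case (12 scales, correlation 0.8, all 55 retained) still falls short of 90% power. These sizes rest on assumed correlations and, for the all-scales figures, on SD 8.6 and margin 6.1 applying to every scale. The single-scale figures at other SDs illustrate sensitivity; the documents give no SD for any scale but treatment burden.

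**What to change.** Name one primary CFQ-R scale and one primary time point, for example 12 months, the end of intervention. Test non-inferiority at one-sided 0.025, read from a two-sided 95% confidence interval, against a margin stated for that scale. Saying this explicitly also reconciles the 0.025 in the Sample size section with the 0.05 in the Data analysis section.

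Treatment burden keeps the current sample size, provided that 6.1 is confirmed as its margin; the article ties only the SD to that domain. If the investigators prefer another scale on clinical grounds, the power should be restated with that scale's SD and margin.

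Make the remaining scales secondary, reported as differences with 95% confidence intervals or tested in a pre-ordered sequence after the primary. State that the 90% power applies to the named scale only.

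The cost is wording in the protocol and SAP and a registry update. No extra participants are needed if treatment burden is chosen and 6.1 stands. The small downside is that the other scales lose confirmatory status. Keeping all 12 as primary would cost more: about 69 per group for 90% power per scale at a Bonferroni level of 0.025/12 = 0.00208, or about 75 to 76 per group for 90% joint power if all must pass (independence and the Bonferroni bound respectively). Both assume SD 8.6 and margin 6.1 throughout, are before any dropout allowance, and already exceed the 55 planned.

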#### Secondary outcome measures

##### Modified shuttle test

The modified shuttle test (MST25) is an externally paced maximal exercise capacity test that has been validated with peak aerobic capacity in children with CF [14]. Our clinic regularly employs the MST as an outcome measure secondary to its high reliability [20] and responsiveness to physiotherapy interventions [21]. Heart rate (bpm), oxygen saturation (SpO_2_ in %), rate of perceived exertion (modified Borg dyspnoea scale) [22], and 15-count breathlessness score [23] will be collect at four timepoints: pre-MST25, immediately post-MST25, 1 min recovery, and 2 min recovery. Distance (metres), level completed and self-reported limiting factor (e.g. breathlessness, leg fatigue) will be collected.

##### Medical record information

A chart review of medical records will be performed to extract medical information such as: hospital, outpatient appointments (face-to-face and/or telehealth), number and type of staff patient seen, and intravenous antibiotic days as well as clinical measurements collected routinely in three monthly MDT reviews: body height, weight, age, spirometry, medication, and relevant social factors (e.g. distance travelled to attend clinic / hospital).

##### Cough and activity questionnaire

Self-reported cough and activity questionnaires will be completed weekly. Parameters of cough frequency, moistness, and colour of sputum will be collected (Additional file 1: Appendix 1).

##### Participation

The CAPE and PAC are questionnaires that measure participation of children in a range of activities outside of school. The CAPE and PAC collects information about the child’s frequency, diversity, and enjoyment of an activity in formal (organised sport, other skill-based activities as well as clubs, groups and organisations) and informal activities (recreational, active-physical, social, skill-based and self-improvement).

##### Quality of care

The Measure of Processes of Care (MPOC) assessment is a validated and reliable questionnaire tool useful in understanding parents’ perceptions of the care they and their children receive (S. M. [15]). The MPOC addresses five aspects of care: Enabling and Partnership, Providing General Information, Providing Specific Information about the Child, Coordinating and Comprehensive Care for the Child and Family, and Respectful and Supportive Care. Data from all five domains will be collected and analysed.

### Cost effectiveness

Economic analysis will be performed from both the healthcare and patient perspective. Costs associated with health care services will be retrospectively retrieved post intervention (e.g. cost of outpatient visits, inpatient admissions, staff time and equipment). Healthcare costs from the patient’s perspective will be calculated using data collected from a chart audit (e.g. number of hospital visits, and services utilised), additional information will be estimated (e.g. costs associated with commuting, time taken off work, and number of family members who accompany the child to clinic). Additional information will be estimated by investigators using published data (e.g. cost of fuel, duration of travel). Incremental cost-effectiveness ratio between the two groups will be calculated using the CFQ-R. Cost per reduction in hospital days will also be analysed if a difference between the two groups is observed.

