**Discussion:**

We anticipate that this multi-modal telehealth service will deliver a comparable service to traditional face-to-face models. An alternative to existing outpatient physiotherapy services may potentially increase patient options for access to care and patient-orientated outcomes such as quality of life. If deemed appropriate, the new model of care can be integrated into clinical practice immediately.

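### The planned cost-effectiveness ratio divides by a CFQ-R difference that the design expects to be small, with no fallback if the arms prove comparable

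*Protocol article*

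**What the plan says.** The Study aim section lists cost-effectiveness beside quality of life and clinical efficacy. The Cost effectiveness section describes costs from the healthcare and patient perspectives and then states: "Incremental cost-effectiveness ratio between the two groups will be calculated using the CFQ-R". No condition is attached, and nothing is said about a CFQ-R difference close to zero. A second ratio is conditional: "Cost per reduction in hospital days will also be analysed if a difference between the two groups is observed".

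On the instrument, the primary outcome section says "It includes nine quality of life domains" "as well as three symptom-based scales", which makes 12 scales, and adds "Scores for each domain will be analysed individually". It defines no total or summary score.

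On the expected result, the Study design section describes a "non-inferiority trial with a 1:1 allocation across two treatment arms". The Background asks whether CyFiT OPS can be non-inferior to Usual OPS. The abstract's discussion paragraph states: "We anticipate that this multi-modal telehealth service will deliver a comparable service to traditional face-to-face models".

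**The concern.** An ICER is a cost difference divided by an effect difference. It is informative when the effect difference is clearly away from zero. A non-inferiority trial is usually run because the new service is expected to be about as good and preferable on other grounds, here access, infection risk and possibly cost. In that case the denominator is close to zero, and the ratio can change sign or become very large through sampling error alone.

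At stake is the usefulness of the economic result. If CyFiT OPS proves comparable, the service will want to know whether it costs less, for the hospital and for families. A cost per CFQ-R unit with an unstable denominator would obscure that answer even if the cost difference were well estimated. With 12 separately analysed scales, there could also be several such ratios of differing sign.

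**Working it through.** **Inputs** (Sample size section unless noted)

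- Difference used for planning: 6.1 points, the MCID ("using distribution/Smallest Error Measurement method) as 6.1").
- SD: 8.6, reported for CFQ-R improvement in treatment burden; using it for other domains is an assumption.
- Power 0.9, alpha 0.025.
- 42 per group, 55 after the dropout allowance; 1:1 allocation (Study design section).
- True CFQ-R difference: not stated. It is taken as 0 in the main case and varied up to 6.1.

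**Reproducing the plan's figure.** n per group = 2 × [8.6 × (1.960 + 1.282) / 6.1]² = 41.77, rounded up to 42. This matches a non-inferiority calculation with margin 6.1, true difference 0 and one-sided alpha 0.025. A two-sided 0.05 superiority calculation for a difference of 6.1 also gives 42, so the figure is compatible with an expected difference of zero but does not prove it.

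**Precision of the denominator.** SE = SD × √(2/n).

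- n = 42: 8.6 × √(2/42) = 1.88 points; 95% half-width 1.96 × 1.877 = 3.68.
- n = 55: 8.6 × √(2/55) = 1.64 points; 95% half-width 1.96 × 1.640 = 3.21.

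**Behaviour of the denominator.** For a true difference d, with Φ the normal distribution function:

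- P(estimate < 0) = Φ(−d/SE)
- P(estimate within 1 point of zero) = Φ((1 − d)/SE) − Φ((−1 − d)/SE)
- A 95% Fieller interval for the ratio is bounded only if the denominator differs from zero at the 5% level: P = 1 − Φ(1.96 − d/SE) + Φ(−1.96 − d/SE)

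Example at d = 0, n = 42: Φ(1/1.877) − Φ(−1/1.877) = 0.406.

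| True difference | Estimate below 0 (n = 42 / 55) | Within 1 point of zero (42 / 55) | Fieller interval bounded (42 / 55) |
|---|---|---|---|
| 0 | 0.50 / 0.50 | 0.41 / 0.46 | 0.05 / 0.05 |
| 1 | 0.30 / 0.27 | 0.36 / 0.39 | 0.08 / 0.09 |
| 2 | 0.14 / 0.11 | 0.24 / 0.24 | 0.19 / 0.23 |
| 6.1 | 0.001 / below 0.001 | 0.003 / 0.001 | 0.90 / 0.96 |

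**Effect on the ratio.** Fix the cost difference at 1,000 units (an arbitrary assumption, with no cost uncertainty) and let the true effect difference be 0. The ratio exceeds x when the estimate falls between 0 and 1,000/x. The 97.5th percentile therefore solves Φ(1,000/(x × SE)) = 0.525, so x = 1,000/(0.0627 × SE). This is about 8,500 per point at n = 42 and 9,700 at n = 55, and by symmetry the 2.5th percentiles are the same values with a negative sign. Uncertainty in costs would widen the spread.

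**The case against.** The strongest reply is that an article condenses a fuller plan. The domain, the time point and the handling of uncertainty are commonly left to an economic analysis plan, and planning an ICER does not exclude a cost-effectiveness plane or net benefit. That stands for the missing domain: on its own it would be omitted detail. A reader might infer that the ratio is undefined or self-contradictory, but analysing domains individually is compatible with one ratio per domain. What remains is that the article commits to the ratio without condition, in a design where its denominator is expected to be small.

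The zero difference is inferred. The abstract also allows that quality of life may increase, and CyFiT OPS adds trackers, monitoring and group sessions. Non-inferiority could be met with a real gain, so the ratio is not bound to fail whenever the trial succeeds. Nor is its interval always unbounded: under equality that happens about 95% of the time, and at a true 6.1 points only 4 to 10% of the time. The protocol also does not call the ICER its headline economic result.

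A reader might further take the conditional hospital-day ratio as selective reporting. The text does not support this. A cost per day reduced needs a reduction, the condition is stated in advance, it does not ask for a large or favourable effect, and it restricts the ratio only. The Medical record information section extracts hospital and intravenous antibiotic data without condition.

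**Conclusion.** The concern holds in a limited form. If the arms are truly close, the planned ratio will usually be too unstable to interpret: under equality its sign is a coin toss and its interval is bounded in about 1 trial in 20. A modest real benefit does not rescue it, since at a true 2 points the interval is bounded in 19 to 23% of trials. Near the full 6.1 points the ratio behaves well (90 to 96%).

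These figures rest on a near-zero true difference read from the non-inferiority framing, on the treatment burden SD applied to whichever domain is used, on a normal approximation, and on 42 to 55 analysed children per group. The point concerns an economic analysis and does not touch the conduct of the trial or its primary clinical conclusion. It is worth correcting because cost-effectiveness is a stated aim and a better-behaved analysis uses the same data.

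**What to change.** In the economic analysis text:

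1. Report the mean cost difference per child, ΔC, with a bootstrap 95% interval, from the healthcare and patient perspectives.
2. Name one CFQ-R domain in advance and report ΔC jointly with the 12-month (end of intervention) difference in that domain, ΔE, on a cost-effectiveness plane, resampling costs and effects together.
3. Report incremental net benefit, λ × ΔE − ΔC, over a stated range of values λ per CFQ-R point. It involves no division, so it stays defined and has a finite interval when ΔE is near zero.
4. Give an ICER only alongside these results.
5. Report the difference in hospital days with its confidence interval whatever its size. The condition on the cost-per-day-reduced ratio may stand.

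The cost is a few sentences and slightly more analysis work. The cost and CFQ-R data are already to be collected.

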## Methods/design

### Study aim

The aim of this study is to investigate the efficacy of a telehealth outpatient physiotherapy service (CyFiT OPS) on patient quality of life, clinical efficacy and cost-effectiveness of healthcare delivery when compared to Usual OPS.

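### The cost per reduction in hospital days is analysed only if the trial happens to observe a difference, and nothing is defined for an increase; the condition should be deleted

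*Protocol article*

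**What the plan says.** Cost-effectiveness is part of the stated aim: the Study aim section covers "clinical efficacy and cost-effectiveness of healthcare delivery when compared to Usual OPS". The Cost effectiveness section plans two ratios.

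- The first carries no condition: "Incremental cost-effectiveness ratio between the two groups will be calculated using the CFQ-R".
- The second does: "Cost per reduction in hospital days will also be analysed if a difference between the two groups is observed".

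The section does not say whether the difference has to be numerical or statistically significant, or whether its direction matters. The only general threshold is in Data analysis: "Statistical significance will be set at *p* < 0.05". That sentence does not mention the economic analysis.

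The Study design section describes a "non-inferiority trial with a 1:1 allocation across two treatment arms". Sample size rests on the CFQ-R alone. No section gives a mean, SD, expected difference or power for hospital days.

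**The concern.** Whether a result is estimated should not depend on the value it takes. Here the observed difference in hospital days opens or closes the analysis that has that same difference as its denominator. The wording also covers one direction only, because a cost per day reduced has no plain meaning if CyFiT increases hospital days.

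At stake is how a published cost per hospital day avoided can be interpreted. A non-inferiority design anticipates a comparable service, so a small or absent difference in days is a case the rule must handle well. That is where selecting on the result does most harm, if the condition selects at all.

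**Working it through.** **1. The plan's own figure.** Inputs from Sample size: difference 6.1, SD 8.6, power 0.9, alpha 0.025 (taken as one-sided).

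n per arm = 2 × SD² × (1.960 + 1.282)² / difference² = 2 × 73.96 × 10.51 / 37.21 = 41.8, rounded up to 42. This matches the article, which then recruits 55 per arm. The standardised difference is 6.1/8.6 = 0.71 SD. Hospital days play no part in the calculation.

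**2. Reading A: any numerical difference.** Hospital days were simulated with no true effect, as zero-inflated negative binomial counts (assumed means 2 to 14, SDs about 4.7 to 19.5; 42 or 55 per arm; 20,000 trials per case). The arm means differed in 99.1% to 99.8% of trials. CyFiT showed a reduction in about 49% to 50%.

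**3. Reading B: p < 0.05, two-sided (sidedness assumed).** Let δ be the true difference in SD units, λ = δ√(n/2) and c = 1.96.

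- Average exaggeration among significant reductions = [λ + φ(c − λ)/(1 − Φ(c − λ))] / λ.
- Example with n = 55 and δ = 0.2: λ = 0.2 × 5.244 = 1.049, φ(0.911) = 0.263 and 1 − Φ(0.911) = 0.181. The ratio is (1.049 + 1.455)/1.049 = 2.4.

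| True difference (SD) | Power, n = 55 | Exaggeration, n = 55 | Power, n = 42 | Exaggeration, n = 42 |
|---|---|---|---|---|
| 0.1 | 8% | 4.6 | 7% | 5.2 |
| 0.2 | 18% | 2.4 | 15% | 2.7 |
| 0.3 | 35% | 1.7 | 28% | 1.9 |
| 0.5 | 75% | 1.2 | 63% | 1.3 |
| 0.71 | 96% | 1.02 | 90% | 1.06 |

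The smallest significant difference is 1.96 × √(2/n): 0.37 SD at n = 55 and 0.43 SD at n = 42. Below that true size every passing reduction is exaggerated. Above it the exaggeration is only an average.

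**4. Reading B with skewed counts.** Assumed: negative binomial days, 55 per arm, Welch t-test, true 20% reduction. SD = √(mean + mean²/dispersion).

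| Mean / dispersion | SD | True days saved | Condition met | Mean days saved if significant | Ratio |
|---|---|---|---|---|---|
| 5 / 0.3 | 9.4 | 1 | 8.5% | 3.82 | 3.8 |
| 10 / 0.5 | 14.5 | 2 | 11.0% | 6.00 | 3.0 |
| 10 / 1.0 | 10.5 | 2 | 19.1% | 4.57 | 2.3 |

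Under the zero-inflated distributions of step 2, with true reductions of 20% to 30% and 42 or 55 per arm, the condition is met in about 6% to 26% of trials. The ratio is then about 1.9 to 5.3.

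**5. From days to cost per day.** No costs were simulated. Suppose, as an illustration, that incremental cost is C − k·d, where C is the programme cost, k the cost of one hospital day and d the days saved. Cost per day avoided is then C/d − k. Replacing d by f·d gives C/(f·d) − k. With C positive this is lower, so it favours CyFiT, but it is not the true value divided by f, and its sign can change.

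**6. An increase under CyFiT.** Reading A has no direction, so an increase meets the condition but has no defined ratio. Under Reading B, a true 30% increase fails to reach p < 0.05 in 76% to 91% of trials (step 4 distributions, 55 per arm).

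**The case against.** Several parts of the other side's case stand.

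- **Under Reading A the condition does no selecting.** If it is met in about 99% of trials, the result is nearly the unconditional analysis. Chance reductions in half of null trials are ordinary sampling error and would remain after the condition is removed. What is left is a condition without a purpose and an undefined result for an increase.
- **Reading B is an inference.** The economic section says observed, not significant. All the exaggeration figures depend on this reading and on assumed hospital-day distributions. A 20% reduction lies in the low-power region, where exaggeration is largest.
- **There may be an innocent reason.** A ratio per day reduced is undefined at zero difference. An unseen analysis plan may define the trigger, although a definition alone would not remove the dependence on the result.

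A reader might also infer three stronger claims that the document does not support.

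- *Only exaggerated effects would be reported.* By step 3 this is strictly true only for true effects below about 0.37 to 0.43 SD. At 0.71 SD the average inflation is 2% to 6%.
- *An increase in hospital days would vanish from the economic analysis.* The Cost effectiveness section counts inpatient admissions as healthcare costs without condition, and the CFQ-R ratio is unconditional too. Extra admissions would raise CyFiT's incremental cost there. Only the separate hospital-days result is lost.
- *Cost per day avoided would be too low by the same factor as the days are inflated.* Step 5 shows that the numerator moves with the days, so the amount depends on the costs.

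**Conclusion.** The point holds in limited form. The sentence makes a supplementary economic result depend on the trial's own outcome, frames it for one direction only, and leaves the trigger open. Neither reading gives a useful rule. The numerical reading filters almost nothing. The significance reading would seldom report modest effects and, when it did, would tend to exaggerate the days saved, by about 2 to 4 times in the step 4 scenarios. CyFiT would then look too favourable by an amount that cannot be stated without cost data.

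The roughly 99% figure varied little across the distributions tried. The 2 to 4 times figure rests on Reading B, a two-sided test, an assumed true 20% reduction, and assumed means of 5 to 10 days with SDs of about 9 to 15. It shrinks as power rises. The primary outcome, the sample size and the CFQ-R ratio are unaffected. Severity is minor.

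**What to change.** Delete the condition. In every case report incremental cost and incremental hospital days, both as CyFiT minus Usual OPS and in whichever direction they fall. Give an interval for each and their joint uncertainty, for example by bootstrap on the cost-effectiveness plane. Quote a cost per hospital day avoided only as a summary of that joint result, whatever the p-value. This also deals with a difference near zero, where the ratio alone breaks down.

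The cost is one sentence of wording and a little extra analysis. The cost and hospital data are already to be gathered retrospectively and by chart review, so no patients or visits are added and the sample size stays at 42 per arm (55 recruited). The small downside is that a wide, uninformative result may be reported where the present rule might report none.
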